## Abstract

**Background:**

Although there have been marked improvements in our understanding of vitamin D functions in different diseases, gaps on its role during pregnancy remain. Due to the lack of consensus on the most accurate marker of vitamin D deficiency during pregnancy and the optimal level of 25-hydroxyvitamin D, 25(OH)D, for its definition, vitamin D deficiency assessment during pregnancy is a complicated process. Besides, the optimal protocol for treatment of hypovitaminosis D and its effect on maternal and neonatal outcomes are still unclear.

**Objective:**

The aim of our study was to estimate the prevalence of vitamin D deficiency in the first trimester of pregnancy and to compare vitamin D screening strategy with no screening. Also, we intended to compare the effectiveness of various treatment regimens on maternal and neonatal outcomes in Masjed-Soleyman and Shushtar cities of Khuzestan province, Iran.

**Methods:**

This was a two-phase study. First, a population-based cross-sectional study was conducted; recruiting 1600 and 900 first trimester pregnant women from health centers of Masjed-Soleyman and Shushtar, respectively, using stratified multistage cluster sampling with probability proportional to size (PPS) method. Second, to assess the effect of screening strategy on maternal and neonatal outcomes, Masjed-Soleyman participants were assigned to a screening program versus Shushtar participants who became the nonscreening arm. Within the framework of the screening regimen, an 8-arm blind randomized clinical trial was undertaken to compare the effects of various treatment protocols. A total of 800 pregnant women with vitamin D deficiency were selected using simple random sampling from the 1600 individuals of Masjed-Soleyman as interventional groups. Serum concentrations of 25(OH)D were classified as: (1) severe deficient (<10ng/ml), (2) moderate deficient (10-20ng/ml), and (3) normal status (>20ng/ml). Those with severe and moderate deficiency were randomly divided into 4 subgroups and received vitamin D3 based on protocol and were followed until delivery. Data was analyzed according to the intention-to-treat principle.

**Results:**

Recruitment commenced in July, 2014, and as estimated, nearly 3.5 years is needed to complete the study. Results of this study will (1) provide reliable information regarding the prevalence of vitamin D deficiency during pregnancy using universal vitamin D screening approach and (2) determine the beneficial effects of universal screening and compare the various treatment protocols in terms of pregnancy outcomes.

**Conclusions:**

Since vitamin D deficiency is a prevalent disorder in pregnancy among Iranian population, this study will ensure creation of reliable evidence-based findings and will enable clinicians to better evaluate and treat vitamin D deficient pregnant women.

**Trial Registration:**

International Standard Randomized Controlled Trial Number (ISRCTN): 2014102519660N1; http://www.irct.ir/searchresult.php?keyword=&id=19660&number=1&prt=7805&total=10&m=1 (Archived by WebCite at http://www.webcitation.org/6p3lkqFdV)

## Introduction

### The Importance and Function of Vitamin D

Vitamin D as a fat-soluble steroid hormone is mainly synthesized by the skin on exposure to ultraviolet light and to a lesser extent can be ingested in the diet. It undergoes hydroxylation in the liver to produce an inactive supply form of 25-hydroxyvitamin D, 25(OH)D. Circulating 25(OH)D gets converted by renal 1-alpha-hydroxylase to the active form of 1,25-dihydroxyvitamin D3 which is the hormonally active form of vitamin D [1]. Since the half-life of 1,25(OH)D is short, circulating 25(OH)D is considered as the primary indicator of vitamin D status [2].

Vitamin D is best known for its effect on calcium hemostasis and bone metabolism [3], and plays a key role in cell differentiation, apoptosis, antiproliferation, immunosuppression, and antiinflammation in different body systems [4-6]. Recent growing evidence confirms its protective influence on the prevention of certain diseases like cancer [7], cardiovascular disorders [8], falls and fractures [9], autoimmunity [10], type-2 diabetes [11], and depression [12].

Although available data suggest the significant role for vitamin D deficiency in women’s reproductive health, the maternal and fetal function of vitamin D during pregnancy is not deeply recognized. One potential role of vitamin D during pregnancy is modulation of immune response [13]; however, evidence shows that it may also have functions on musculoskeletal [14] and cardiovascular systems [15] as well as neural development of the fetus [16]. Moreover, studies report a significant association between maternal vitamin D status and neonatal serum levels [17].

With respect to maternal vitamin D deficiency and adverse pregnancy outcomes, data are inconclusive and need further investigations. Trials have reported lower risk of preeclampsia and gestational diabetes in women receiving vitamin D supplementation compared with no intervention or placebo groups [18,19].

In terms of neonatal outcomes, data suggest reduced risk of preterm birth and low birth weight of less than 2500 grams in women who received vitamin D supplements. Interestingly, several observations have reported the influence of maternal vitamin D status beyond the postnatal period and have found its significant effect on childhood development and growth [20,21]. In regard with other pregnancy outcomes like mode of delivery, infant death, or neonatal biometric parameters, findings are not definite [22].

In recent years, the prevalence of vitamin D deficiency has increased and it is now recognized as a common global health concern and an ongoing pandemic [23]. Moreover, low levels of vitamin D during pregnancy have been reported in many populations worldwide, even in those with abundant sun exposure [24]. Previous findings have reported a varied prevalence of 18 to 84% for hypovitaminosis D during pregnancy, depending on the population studied [25-28]. Its prevalence among certain high-risk groups of pregnant women, particularly those with Middle Eastern origin like Iranian women (with low dietary vitamin D intake, high prevalence of pregestational obesity, and limited sun exposure) has been estimated to be approximately 60-80% [29-31]. However, due to the lack of consensus on the most accurate marker and test of vitamin D deficiency during pregnancy, and the optimal level of 25(OH)D for its definition, vitamin D deficiency assessment during pregnancy is a complicated process [32]. Furthermore, the comparison of vitamin D deficiency among different populations seems relatively troublesome due to the diversity of definitions, heterogeneity of the studied groups, or seasonal variations.

### Knowledge Gap

Although advising vitamin D consumption may prevent hypovitaminosis D in pregnant women, at this time there is insufficient evidence to support a recommendation for screening all pregnant women for vitamin D deficiency, and its beneficiary impact on pregnancy outcomes has not been well established. Besides, the optimal required dose during pregnancy is still undefined. In this respect, there is little population-based data available to quantify the treatment of vitamin D deficiency in pregnancy. In addition, the lack of high-quality evidence has hampered the implementation of vitamin D deficiency prevention programs and treatment protocols. Furthermore, there exists scarce data from Iranian population on the prevalence of gestational hypovitaminosis D.

### Clinical Endpoints

Primary endpoints are to find out the beneficiary impact of screening of pregnant women for vitamin D deficiency on pregnancy and neonatal outcomes and assessing the effect of supplementation with vitamin D on these outcomes. In the screening group, within the framework of randomized controlled trial, the endpoint was cord serum concentration of 25(OH)D to compare various doses, regimen, and routes for vitamin D supplementation in pregnancy.

In this regard, primary outcomes are gestational diabetes, preterm delivery, and pregnancy induced hypertension. Secondary outcomes are type of delivery and neonatal outcomes including birth weight (gr); head circumference (cm), height (cm); appearance, pulse, grimace, activity, respiration (APGAR) score 1, 5 minute, icterus, cord falling off time (day), serum calcium concentration (mg/dl), and cord levels of 25(OH)D (ng/ml).

### Research Questions

The questions are as follows: (1) How is the status of vitamin D among pregnant women in Khuzestan? (2) Is vitamin D deficiency related to adverse maternal and neonatal outcomes in pregnancy? (3) Does supplementation with vitamin D improve maternal and neonatal outcomes? (4) Is there any difference between various doses, regimen, and route for vitamin D supplementation in terms of pregnancy outcomes? (5) Taken altogether, is it reasonable to advise universal vitamin D deficiency screening program to detect and treat vitamin D deficiency in pregnancy?

## Methods

### Overall Study Design

This was a 2-phase population-based study. The first phase comprised a population-based cross-sectional study in which 1600 and 900 first trimester pregnant women attending health centers of Masjed-Soleyman and Shushtar, Khuzestan province, Iran were recruited using stratified multistage cluster sampling with probability proportional to size (PPS) method [33]. In the second phase of this study, within the framework of screening regimen, Masjed-Soleyman participants with vitamin D deficiency were assigned to a screening program versus Shushtar participants (as nonscreening arm) to assess the effectiveness of various treatment regimens. Pregnancy outcomes including preterm delivery, miscarriage, preeclampsia, gestational diabetes, and type of delivery and neonatal outcomes including birth weight (gr), head circumference (cm), height (cm), APGAR score 1, 5 minute, icterus, cord falling off time (day), serum calcium (mg/dl) level, and cord concentration of 25(OH)D (ng/ml) were recorded.

Shushtar participants (as nonscreening arm) served as controls and were followed till delivery and any adverse pregnancy outcomes were assessed.

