### Subject Recruitment and Eligibility Criteria

Pregnant women, aged 18-40 years, were eligible if they had gestational age <14 weeks based on last menstrual period or obstetrical estimation, singleton pregnancy, and had planned to receive ongoing prenatal and delivery in the Masjed-Soleiman. Participants were excluded if they consumed multivitamins containing more than 400 international unit (IU) per day of vitamin D3; used anticonvulsants; and had history of chronic diseases like diabetes, hypertension, renal dysfunction, liver diseases, and complicated medical or obstetrical history.

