### Data Collection and Quality Control Procedures

At first, midwives responsible for prenatal care in the selected health centers were invited to attend a workshop designed for explaining the study objectives and procedure. Thereafter, first trimester pregnant women seeking maternity care during their first routine prenatal visit were invited to participate in the study after providing a detailed explanation of the study procedure; they signed a written informed consent during recruitment covering all trial procedures and data collection. For gestational age calculation, the first day of the last menstrual cycle (LMP) for women with regular cycles and ultrasonography for those with irregular cycles or those who could not precisely recall their LMP was used. Pregnant women received prenatal care and each adverse pregnancy outcome was managed according to the standard guidelines. At enrollment, for each participant a questionnaire that included information on sociodemographic, anthropomorphic, behavioral, and reproductive characteristics was completed by a trained interviewer.

Weight was measured with minimum clothing to the nearest 100 grams. Height was measured with a tape measure in standing position with normal posture of shoulders. Body mass index was calculated by dividing weight (kg) on height (m^2^). Systolic and diastolic blood pressures (SBP and DBP) were measured twice in a sitting position with a standard mercury sphygmomanometer after a 15-min rest and the mean of the 2 measurements was considered as SBP or DBP.

A fasting blood sample (5cc) was taken by venipuncture from the antecubital vein. Plasma was then separated by centrifugation (1500g, 10 min, 4˚C) in the central laboratory of Masjed-Soleyman and stored at −20˚C until analysis at the end of the week. Serum concentrations of 25(OH)D for the participants of Masjed-Soleyman were measured immediately, and subsequently their vitamin D status was determined (Table 1). The samples in Shushtar laboratory were stored at −80˚C until the end of the study; finally their serum concentration of vitamin D was measured.

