### Definition of Study Outcomes

In this study the primary outcome was vitamin D deficiency measured as serum level of 25(OH)D and was categorized as: (1) severe deficient (<10ng/ml), (2) moderate deficient, (10-20ng/ml), and (3) normal status (>20ng/ml) [36].

Our secondary outcomes were as follows: Preterm delivery was considered as birth at less than 37 completed weeks of gestation [37]. Miscarriage was referred to as pregnancy loss prior to 20 weeks from LMP [38]. Preeclampsia was defined as systolic blood pressure >140 mmHg or diastolic blood pressure ≥90 mmHg and 24-hour proteinuria ≥0.3 g, started at >20 weeks [39]. Gestational diabetes mellitus referred to glucose intolerance first detected during pregnancy and was diagnosed according to the *International Association of the Diabetes and Pregnancy Study Groups (IADPSG)* criteria [40]. Premature rupture of membrane was considered as rupture of the fetal membranes before the onset of labor regardless of gestational age [41]. By type of delivery, we meant cesarean section or vaginal delivery. Birth weight (gr) was defined as weight at birth irrespective of gestational age [42].

APGAR score comprises 5 components including *appearance, pulse, grimace, activity, and respiration*, each of which is given a score of 0-2 and reported at 1 and 5 minutes after birth [43]. Neonatal icterus was defined as the yellowish discoloration of skin and sclera by bilirubin, usually first noted in the face and then the body [44]. Cord falling off time (day) is the separation time of remained umbilical cord after birth [45].

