**Occupation**										
	Worker	14	1.60	21	2.30	35	1.90	.46
	Clerk	135	15.00	119	13.20	254	14.10	
	Self-employed	111	12.30	117	13.00	228	12.70	
	Housewife	640	71.10	643	71.40	1283	71.30	
	Total	900	100.00	900	100.00	1800	100.00	

^a^The chi-square statistic is significant at the .05 level.

^b^Fisher exact test results is significant at the .05 level.

For the second phase of the study, as statistically was calculated, we needed 800 women, therefore the remaining women were referred to a specialist for further treatments. However, in terms of baseline features except for vitamin D levels, there was no significant difference between the initial sample in Masjed-Soleyman and those who were allocated to intervention (Table 4). The difference for vitamin D is ignorable though.

**Table 4 table4:** Comparison of baseline characteristics between the initial sample of Masjed-Soleyman participants and those allocated to intervention.

Baseline variables	Initial sample (n=1581)	Allocated for intervention (n=900)	*P* value^a^
Age (year)	29 (25-32)^b^	29 (25-32)	.77
First pregnancy age (year)	20 (18-22)	20 (18-22)	.94
First delivery age (year)	20 (18-22)	20 (18-22)	.73
Gestational age (week)	10 (9-12)	10 (9-12)	.97
Vitamin D	11.9 (8-17)	11.2 (7-16)	.01
Number of children	^b^1 (0-2)	1 (0-2)	.67
Gravity	2 (1-3)	2 (1-3)	.62
Parity	1 (0-2)	1 (0-2)	.47
Number of abortions	0 (0-0)	0 (0-0)	.94

^a^*P* value obtained from nonparametric Mann-Whitney test for nonnormal variables.

^b^Median (interquartile range, Q1-Q3).

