### Limitations

However, this study is subject to some limitations. First, conducting the study in urban regions restricts its generalizability to rural areas. Second, some pregnancies may be aborted prior to entering the study and hence it could decrease our power to interpret the results of miscarriage outcome. Third, the potential number of our lost to follow-up cases may be another limitation. Finally, fourth is the concern of vitamin D consumption or lack of adherence to the treatment regimen among the intervention groups.

Overall, the results of this study regarding vitamin D deficiency prevalence and optimal supplementation and treatment methods during pregnancy will empower clinicians with novel recommendations in patient decision-making.

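### If the treated Masjed-Soleyman women are the set compared with Shushtar on miscarriage, losses between first visit and allocation risk being missed in the treated group only

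*Protocol article*

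**What the plan says.** **Outcome.** Overall Study Design lists what is recorded: "Pregnancy outcomes including preterm delivery, miscarriage, preeclampsia, gestational diabetes, and type of delivery". Definition of Study Outcomes places miscarriage among the secondary outcomes and fixes the end of its window: "Miscarriage was referred to as pregnancy loss prior to 20 weeks from LMP". Neither section says when counting starts.

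**Entry.** Under Data Collection and Quality Control Procedures, "first trimester pregnant women seeking maternity care during their first routine prenatal visit were invited to participate in the study". Women "were eligible if they had gestational age <14 weeks" (Subject Recruitment and Eligibility Criteria). Tables 2 and 4 give a median of 10 weeks (IQR 9 to 12) for each city, for the initial Masjed-Soleyman sample and for the allocated women.

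**Shushtar after entry.** Samples are frozen and assayed at the end of the study. The women are not classified or allocated during pregnancy: "Shushtar participants (as nonscreening arm) served as controls and were followed till delivery and any adverse pregnancy outcomes were assessed".

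**Masjed-Soleyman after entry.** Samples are "stored at −20˚C until analysis at the end of the week", although the same section and Blood Assessments also describe the measurement as immediate or prompt. Deficient women are then selected and randomised. The time from assay to allocation is not stated.

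**Who is compared.** Overall Study Design sets Masjed-Soleyman participants with vitamin D deficiency against Shushtar. The Abstract (Methods) and The Second Phase set Masjed-Soleyman participants, without that restriction, against Shushtar.

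**The concern.** A woman can belong to a treatment arm only if her pregnancy has survived the wait for assay, classification and allocation. No such condition applies to a Shushtar woman after her first visit. If allocated women are compared with all enrolled Shushtar women, the treated side has a stretch of guaranteed survival at the early end of a window of roughly 10 weeks (immortal-time bias).

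The direction is fixed: treatment looks better than it is. Intention-to-treat analysis does not cure this, because it preserves groups from allocation onward and the losses in question come before allocation. A larger sample does not cure it either. What is at stake is a favourable miscarriage result feeding into the article's fifth research question, whether universal screening is justified, when supplementation may have had no effect on it.

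**Working it through.** The plan has no figure of its own to reproduce: it gives no miscarriage rate and no count of losses before allocation. The check has two parts.

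**1. Which set is likely to be compared?**

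- Overall Study Design names deficient women against Shushtar. The Abstract and The Second Phase name all participants.
- Tables 2 and 3 compare 900 Masjed-Soleyman women with 900 Shushtar women. Table 4 gives 1581 in the initial Masjed-Soleyman sample and 900 allocated for intervention.
- Vitamin D, median (IQR), for Masjed-Soleyman is 11 (7-16) in Table 2. In Table 4 it is 11.2 (7-16) for the allocated women and 11.9 (8-17) for the initial sample. The 900 in Table 2 therefore look like the allocated set.
- This is suggestive, not proof. The text says 800 were allocated, and the article does not explain the difference from 900.
- Follow-up to delivery is described for allocated women, women with normal vitamin D and Shushtar. Deficient women who were not allocated were referred to specialists, with no outcome follow-up described.

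**2. How large could the bias be with no true effect?**

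Inputs from the article: entry at about week 10 (Tables 2 and 4); window closes at week 20; assay at the end of the week. A weekly batch means a wait of at most about 1 week, and about half a week on average if blood draws are spread evenly.

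Assumptions: Shushtar losses are counted from the first visit, treated losses from allocation, and the hazard shapes are as below.

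Share of week 10-20 losses falling within a lag of *d* weeks:

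- flat hazard: *d*/10
- hazard halving every *h* weeks: (1 − 0.5^(*d*/*h*)) / (1 − 0.5^(10/*h*))

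For a rare outcome the spurious risk ratio is about 1 minus that share.

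| Lag *d* | Flat | *h* = 4 | *h* = 2 |
|---|---|---|---|
| 0.5 week: share | 5% | 0.0830/0.8232 = 10% | 0.1591/0.9688 = 16% |
| 0.5 week: risk ratio | 0.95 | 0.90 | 0.84 |
| 1 week: share | 10% | 0.1591/0.8232 = 19% | 0.2929/0.9688 = 30% |
| 1 week: risk ratio | 0.90 | 0.81 | 0.70 |

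**Cross-check without the rare-outcome approximation.** Assume a risk from week 10 to week 20 of 2%, 4% or 6%, 800 treated and 900 Shushtar women, and a hazard that is flat or falls as exp(−0.3) per week.

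- Half-week lag: 0.8 to 2.5 losses missed per 800 (flat) or 2.4 to 7.2 (falling). The risk ratio is 0.95 (flat) or 0.85 to 0.86 (falling).
- 1-week lag: 1.6 to 4.9 losses missed (flat) or 4.4 to 13.4 (falling). The risk ratio is 0.90 (flat) or 0.73 (falling).
- With a two-sided 5% test (the article does not state sidedness), the chance of a significant result favouring treatment at a 1-week lag is about 5% to 31%. Without bias it would be 2.5%.

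**The case against.** The strongest reply is that the article never says losses before allocation are dropped, and never says when counting starts in either city. Consent at recruitment covers data collection, and the Abstract and The Second Phase describe a screening arm made up of Masjed-Soleyman participants as a whole. On that reading time zero is enrolment in both cities, and a loss before allocation counts in the screened arm. This stands, and it is why the point is conditional on the analysis set. It does not dispose of the point: Overall Study Design names the other set, the baseline tables appear to use it, and no follow-up is described for unallocated deficient women.

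A second reply is that the lag may be very short. This stands in part. The assay wait is at most about a week and may be shorter, and the rest of the interval is unreported. A reader might infer risk ratios as low as 0.48 by assuming a 2-week lag with a hazard halving every 2 weeks. The article supports neither assumption.

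A third reply is that time origins belong in the analysis plan. In general they do. Here, however, the article itself states two comparison sets, and one of them is exposed to the bias.

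A reader might also fault the Limitations section, which says "some pregnancies may be aborted prior to entering the study and hence it could decrease our power to interpret the results of miscarriage outcome". That remark concerns pregnancies lost before enrolment, which can happen in either city. It does not address the interval from enrolment to allocation, and it is not an error on this point.

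**Conclusion.** The point holds conditionally. If allocated women are compared with Shushtar on miscarriage from different starting points, the result is biased toward benefit: a risk ratio of about 0.95 to 0.84 for a half-week lag and about 0.90 to 0.70 for a 1-week lag, with no true effect. These figures rest on assumed hazard shapes and on counting treated women from allocation. The true lag cannot be determined from the article.

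It would go too far to say that early losses are in fact missed; the documents show only that they risk being missed. The scope is one secondary outcome, absent from the list in Clinical Endpoints. The randomised comparisons among the eight arms share a time zero at allocation and are unaffected. Later outcomes such as gestational diabetes and preterm delivery are barely touched. The remedy is cheap and removes a bias of known direction, so the change should be made.

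**What to change.** State one comparison set for miscarriage and one start of follow-up for both cities, by either route:

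- **All enrolled women.** Compare everyone enrolled in each city from the first visit, and count losses before allocation in the screened arm. This needs outcomes for the deficient women who were referred and not allocated, which may not be available.
- **Common landmark.** Start both cities at the same interval after the first visit, for example the median time from visit to allocation. Exclude losses before it in both cities, and count treated women allocated later than the landmark only from their allocation.

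Reconcile Overall Study Design with the Abstract and The Second Phase on who forms the screening arm, and report the time from first visit to allocation.

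Cost: a change to analysis wording, with no new recruitment or treatment; the Results section says the study is at the data-analysis stage. The landmark route drops a few early events. Both routes depend on dates: losses must be datable from the first visit, and the landmark route also needs allocation dates. The article does not confirm that these were recorded.
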